### Interim analyses {21b}

An interim analysis will be performed on the primary endpoint after the first cohort (*n* = 20) of patients has been randomized and has completed the 3-month follow-up. The interim analysis will be performed by an independent statistician blinded to the treatment allocation and will report their findings to the project leaders ([name] and [name]). Statistical results will determine whether the trial should be continued, modified, or halted earlier.

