## Statistical methods

### Statistical methods for primary and secondary outcomes {20a}

We will use an intent-to-treat approach to analyze all available data at baseline, post-treatment, and 3 months. We will compare the baseline demographic and clinical characteristics of the groups using the independent *t*-test for continuous variables and chi-square tests for categorical variables. The primary endpoint is change in RMQD during 3 months. Analyses of the primary and secondary continuous outcome variables will be analyzed using two-way repeated-measures ANOVA. The effect sizes of the mean group differences will be calculated as the Cohen *d*. Differences with a 2-sided *P*-value < 0.05 will be considered significant. All data will be analyzed using IBM SPSS Statistics V.22.

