#### Composition of the data monitoring committee, its role, and reporting structure {21a}

A Data Monitoring Committee (DMC) is not needed, because our trial is of short duration and with known minimal risks. But the researchers ([name] and [name]) will regularly analyze the data to make adjustments.

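### Outcome results from the first 20 patients decide whether the trial continues, changes or stops, with no criterion and almost no information behind the decision

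*Protocol article*

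**What the plan says.** Under Interim analyses {21b}: "An interim analysis will be performed on the primary endpoint after the first cohort"; the timing is "after the first cohort (*n* = 20) of patients has been randomized and has completed the 3-month follow-up". On who does it and who receives it: "The interim analysis will be performed by an independent statistician blinded to the treatment allocation and will report their findings to the project leaders". On its use: "Statistical results will determine whether the trial should be continued, modified, or halted earlier". The section gives no efficacy threshold, no futility criterion and no limit on what may be modified.

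Under Composition of the data monitoring committee {21a}: "A Data Monitoring Committee (DMC) is not needed, because our trial is of short duration and with known minimal risks". The next sentence says that researchers "will regularly analyze the data to make adjustments". The number, content and blinding of these analyses are not stated.

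The only significance rule is in Statistical methods for primary and secondary outcomes {20a}: "Differences with a 2-sided *P*-value < 0.05 will be considered significant". Sample size {14} uses the full two-sided 0.05 with 80% power and makes no allowance for interim looks.

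**The concern.** The protocol makes a comparison of about 10 patients per arm decisive for the trial's future. So small a look is a poor basis for either kind of stop. An efficacy stop would rest on an exaggerated estimate and would use up type I error that the final test also claims in full. A futility stop would end a worthwhile trial by chance. The open permission to modify the trial, and the further regular analyses made in order to adjust it, extend the problem beyond this one look. There is no independent committee between the results and the people who run the trial.

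**Working it through.** **Inputs.** From Sample size {14}: mean RMDQ changes 5.5 (SD 4.7) and 3.1 (SD 4.8), so the design difference is 5.5 − 3.1 = 2.4; two-sided alpha 0.05; power 80%; 66 evaluable per arm; 20% dropout; 83 per arm, 166 in total. From Interim analyses {21b}: 20 patients, about 10 per arm at 1:1. From Recruitment {15}: eight waves of 20. The check uses the two-arm comparison of mean change on which the sample size rests.

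**The plan's own figure.** Pooled SD = √((4.7² + 4.8²)/2) = 4.75. The normal formula gives n = 2 × [4.75 × (1.960 + 0.842)/2.4]² = 61.5, so 62 per arm. The exact t-test gives 63, or 64 with SD 4.8 in both arms. Multiplying 63 by π/3 (the Mann–Whitney adjustment) gives 66. Dropout: 66/0.8 = 82.5, so 83 per arm and 166 in total, as stated. The sample size is not in question here.

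**Information at the look.** 20/166 = 0.12 of the enrolled target; 20/132 = 0.15 of the evaluable target.

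**What 10 per arm can show.**
- SE of the difference = √((4.7² + 4.8²)/10) = 2.12.
- Smallest significant observed difference = t(0.975; 18 df) × SE = 2.101 × 2.124 = 4.46 points, which is 1.86 times the design effect.
- Power for 2.4 points (noncentral t, 18 df) = 18.8%. With 8 per arm after 20% dropout it is 15.6%.
- Probability of a wrong-sign estimate when 2.4 is true = Φ(−2.4/2.124) = 0.129.
- Probability of an estimate below half the design effect = Φ((1.2 − 2.4)/2.124) ≈ 0.29.
- Simulated estimates that reach significance at this look average about 5.3 points in size, more than twice the true 2.4.

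**If the look is used for efficacy.** Take P < 0.05 at the interim and again at the end, with correlation √0.12 = 0.35 between the two statistics. The bivariate normal calculation gives an overall two-sided type I error of 0.094 (0.093 at information 0.15). Simulated t-tests agree (0.094 with 83 per arm at the end, 0.093 with 66).

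**If the look is used for futility.** Type I error does not rise, but power falls. At 66 per arm, simulated power is 82% with no interim, 74% if the trial halts on a wrong-sign estimate, and 62% if it halts on an estimate below half the design effect. Both halting rules are illustrations; the protocol states neither.

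**Regular looks (illustration).** Assume one between-arm test at 0.05 after each of the eight waves (10, 20, …, 80 per arm). Simulated type I error is 0.177, or 0.182 with a final test at 83 per arm. The protocol does not state this schedule.

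**After the fix.** With no between-arm decision at the look, type I error stays at 0.050. With interim P < 0.001 and final P < 0.05 it is 0.051.

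**The case against.** The strongest defence has four parts.

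1. **Boundaries often sit in a SAP or full protocol, and neither is shown.** This stands as far as it goes: a missing numerical boundary would not carry the point alone. But the article positively fixes the timing, the endpoint, the recipients and the decisive role of the result. No boundary added elsewhere can make 10 per arm informative.

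2. **Inflation of type I error is conditional.** This stands. The 0.05 rule is in the general analysis section and is not tied to the interim. A reader might infer that the trial will run at 9% or 18%. The documents do not say so: the first figure needs an efficacy stop at 0.05, and the second also needs a schedule of looks that is assumed here.

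3. **The interim statistician is independent and blinded.** This also stands. A reader might infer that the interim unblinds the leadership, or that it contradicts the blinding described under {17a} and {18a}. Neither is shown. The form of the findings (pooled, coded or by arm) is not stated, and {21a} does not say that the researchers see allocation. Disclosure of the trend to the leadership during recruitment is a risk, not a stated fact.

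4. **The regular analyses may be harmless checks.** They may be, but their stated purpose is to make adjustments, and the text does not restrict them.

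It would also go too far to call the interim decision a coin toss. Under the design effect the estimate has the wrong sign 13% of the time and is non-significant 81% of the time. Nearly uninformative is the accurate description.

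**Conclusion.** The point holds in this form: a stated rule lets primary-endpoint results from about 10 patients per arm determine the course of the trial, without a criterion, while further unspecified analyses are allowed for making adjustments. On the protocol's own difference and SDs, the look has 19% power and needs about 4.5 observed points for significance. Type I error is uncontrolled rather than shown to be inflated. The figure of about 9.4% rests on the 0.05 rule being used for efficacy at both looks. The figure of about 18% rests on an assumed look per wave. Futility use costs power instead, by an amount that depends on a rule the protocol does not give. Because following the text as written can harm the confirmatory result in either direction, and the remedy is simple, it should be corrected.

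**What to change.** **Interim analyses {21b}.** Limit the first-cohort review to pooled, non-comparative items: recruitment, retention, pooled RMDQ SD and safety. State that no between-arm efficacy or futility decision is made, so that the final test keeps 0.05. If an efficacy stop is to stay, require interim P < 0.001 and have the independent statistician hold the comparative results.

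**Data monitoring committee {21a}.** Restrict the regular analyses to pooled data-quality and safety checks.

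**If the look has already been taken,** report it and any decision based on it. This is possible. Trial status gives April 15, 2021 as the first day of recruitment and August 30, 2021 as the date of version 5. A patient enrolled on the first day would reach week 16 on August 5, 2021. Whether the whole first wave had done so is not stated.

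**Cost.** Rewording of two sections through the amendment route that the protocol describes, and the loss of an early efficacy stop that had about 19% power. Rewording cannot undo a look already taken.

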### Methods for additional analyses (e.g., subgroup analyses) {20b}

Changes in the primary outcomes (RMDQ and NRS) will be correlated with other results (deep trunk muscle function, brain function, and potential mediators) to identify the reasons behind any change in the primary outcomes.

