### Eligibility criteria {10}

Participants aged 18 to 60 years whose back pain has persisted for at least 12 weeks and are interested in participating in the trial will be recruited. Table 1 lists the exclusion criteria and the rationale for each criterion. The main screening criteria will be included in the registration questionnaire. We will contact possible eligible participants by telephone or WeChat and invited them to the hospital for final inclusion. In addition, if the participant does not receive treatment at the beginning or does not provide feedback data, we will define it as a drop out.

**Table 1 Tab1:** Exclusion criteria

Exclusion criteria	Rationale
Low back pain has lasted < 3 months	Not NCLBP.
There were clear “red flag signs” (unilateral leg pain and numbness consistent with nerve distribution, musculoskeletal-originated pain, intermittent claudication, weight loss without an obvious cause, back pain at night, trauma, etc.)	Our interventions may not be effective.
The history of spinal surgery	Back problem is complicated by medical or medicolegal issues.
A score < 4 on Roland-Morris Low Back Pain and Disability Questionnaire (RMDQ)	Back pain too mild to detect improvement.
Patients who practice meditation regularly (weekly) in past 3 months	Possible bias due to current or recent interventions.
Patients who participated in courses related to core stability exercises in the past 3 months	Possible bias due to current or recent interventions.
Conditions that may be uncontrolled for self-compassion meditation (e.g., psychosis, major depression or anxiety, current self-harm, or suicidal ideation)	Condition would make it difficult to control or cause harm to participants.
Unable to independently complete Chinese language questionnaires	Condition would make it difficult to communicate.

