### Outcomes {12}

Participants will complete the outcome assessment at baseline, the end of the 4th week, and the follow-up 16 weeks after baseline evaluation. Baseline data collection included demographic and clinical characteristics, such as gender, age, work status, height, weight, education, treatment history, and medical history. Participants scanned the QR code to complete the questionnaire by themselves.

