#### Potential mediators

The clinical effect of low back pain may be mediated by different variables, and the effects of all potential mediators on the outcomes will be explored in both treatment groups. The potential mediators of outcome will be assessed at baseline and at 4 and 16 weeks after randomization with brief screening questions for pain catastrophizing, as well as pain acceptance, self-compassion, and self-efficiency.

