### Sample size {14}

Sample size calculation will be based on the results of our pilot study [34]. We found a mean difference of 5.5 for RMDQ with a standard deviation of 4.7 in the intervention group and a mean difference of 3.1 with a standard deviation of 4.8 in the control group at 16-week follow-up. To detect it at 16 weeks with a two-sided significance level (alpha) of 0.05 and a power of 80% with equal allocation to two arms, it would require 66 patients in each arm of the trial. To allow for 20% drop out, future study must include at least 166 participants (83 in each group). The calculation was performed with the PASS software(version 15).

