### Methods in analysis to handle protocol non-adherence and any statistical methods to handle missing data {20c}

We will use an intent-to-treat approach to analyze all available data; all participants will be assessed at baseline prior to randomization, so for the missing data, we will use the methods of the last observation carried forward or baseline observation carried forward to fill up.

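### Carry-forward filling, if it reaches the mechanism correlations, can produce a spurious link between change in outcome and change in mediator

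*Protocol article*

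**What the plan says.** The section on additional analyses {20b} states that "Changes in the primary outcomes (RMDQ and NRS) will be correlated with other results", which it lists as deep trunk muscle function, brain function and the potential mediators. The stated purpose is explanatory: "to identify the reasons behind any change in the primary outcomes".

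The missing-data section {20c} sets a general rule: "for the missing data, we will use the methods of the last observation carried forward or baseline observation carried forward to fill up". It does not choose between the two methods and exempts no analysis.

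Outcomes and mediators share a schedule. For outcomes: "Participants will complete the outcome assessment at baseline, the end of the 4th week, and the follow-up 16 weeks after baseline evaluation". For mediators: "The potential mediators of outcome will be assessed at baseline and at 4 and 16 weeks after randomization".

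The eligibility section {10} defines drop-out: "if the participant does not receive treatment at the beginning or does not provide feedback data, we will define it as a drop out". Such a person may have baseline data only. The sample size section {14} sets the allowance: "To allow for 20% drop out".

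**The concern.** A missed questionnaire visit usually removes the outcome and the mediator together. If both are filled with their baseline values, the participant's change is zero on both. This happens under baseline carry-forward, and under last-observation carry-forward when there is no week-4 value. If the other participants improve on average on both measures, the filled participants form a cluster at (0, 0), away from the main cloud. That cluster adds positive covariance between the two improvements even when they are unrelated among participants who were observed.

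The mechanism analysis is meant to say why patients changed, so drop-out could be reported as mechanism. This differs from the usual objection to carry-forward, which concerns bias in the difference between arms. The artefact here arises inside each arm and with equal drop-out. A better model for the primary comparison would not remove it if the correlations still used filled data.

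**Working it through.** **The plan's own figure.** The article gives no figure for the correlations, but its drop-out inflation reproduces: 66 / (1 − 0.20) = 82.5, rounded up to 83 per arm, 166 in all. With 2 × 66 = 132 evaluable, 166 − 132 = 34 are allowed to drop out, 17 per arm.

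**Inputs from the sample size section {14}.** RMDQ change, read as change from baseline: 5.5 (SD 4.7) in the combined arm and 3.1 (SD 4.8) in the control arm.
- Pooled mean = (5.5 + 3.1)/2 = 4.3.
- Pooled SD = √[(4.7² + 4.8²)/2 + 1.2²] = √(22.565 + 1.44) = 4.90.
- Standardised mean change a = 4.3/4.90 = 0.88. Within arms, a = 5.5/4.7 = 1.17 (combined) and 3.1/4.8 = 0.65 (control).

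**Input not in the article.** The standardised mean change b of a mediator is not given. It is assumed to lie between 0.3 and 1.0 SD, with 0 as a limiting case.

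**Formula.** Let a share d be filled at (0, 0), and let the two changes be independent with SD 1 in the rest. The covariance is d(1 − d)ab and the variances are (1 − d)(1 + da²) and (1 − d)(1 + db²). Hence

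r = d·a·b / √[(1 + d·a²)(1 + d·b²)].

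For d = 0.20, a = 0.88, b = 0.8: r = 0.140/√(1.154 × 1.128) = 0.12.

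**Results, arms pooled, n = 166, two-sided 5% test, false-positive rates by simulation:**

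| b (assumed) | induced r, 34 filled | false positives, 34 filled |
|---|---|---|
| 0 | 0.00 | 6–7% |
| 0.3 | 0.05 | 11% |
| 0.5 | 0.08 | 20% |
| 0.8 | 0.12–0.13 | 38% |
| 1.0 | 0.15 | 50% |

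**Within arm (17 of 83 filled).** Combined arm: 16% at b = 0.5 and 44% at b = 1.0. Control arm: 11% and 19%. Adjusting the pooled correlation for arm does not remove the artefact.

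**Fewer baseline fills.** If half the drop-outs are baseline-filled and the others carry week-4 values forward, the rate is about 7% to 18% for b from 0.3 to 1.0. If all drop-outs have week-4 values carried forward, it is about 5%.

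**Check of the remedy.** Using only about 132 observed pairs, with the same mean mediator change in both arms, mean r is 0.00 and the false-positive rate about 5%. If the arms differ in mediator change (assumed 0.8 against 0.3 SD), observed pairs pooled over arms still give r = 0.06 and about 10% false positives. Adjusting for arm returns this to 5%.

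**The case against.** The strongest case against is about what the text commits to.

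- **Changes or levels.** Section {20b} speaks of changes in the primary outcomes but of other results without qualification. If baseline values of those results were meant, there would be no cluster at (0, 0). It also does not say that filled values are used; that follows only from reading {20c} as general. This stands as a condition on the point.
- **Filling every drop-out with baseline is close to the worst case.** Last observation is named first, and baseline may be meant only where nothing later exists. The deposit scheme {18b} returns 80 of its 100 yuan at the second follow-up, which encourages attendance at week 16. This stands, and is why the smaller scenarios are given.
- **Joint missingness is not certain for every measure.** Questionnaires are self-completed by QR code, while fMRI and ultrasound need attendance. Someone with RMDQ observed and imaging missing adds no covariance if their mean RMDQ change equals that of the others. The point is therefore firmest for the questionnaire mediators.
- **Some drop-outs never start treatment.** If they truly do not change, zero is near their real value and the assumption of no association does not describe them. This stands in part. The correlation would then reflect who took part, which is still not the mechanism being sought.

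A reader might infer that the correlations will show a mechanism where none exists, always with the hypothesised sign and with several times the nominal error in every test. The documents do not support that. The sign follows the product of the two mean changes, the effect vanishes when the mediator does not move on average, and most null tests in the scenarios with b up to 0.8 remain non-significant.

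**Conclusion.** The point holds as a conditional one: carry-forward filling can produce a spurious correlation in the mechanism analysis. It requires that filled values enter the correlations, that the other results are analysed as changes, that some participants are baseline-filled on both measures, and that both measures change on average. The direction is then usually the hypothesised one.

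The induced correlation is small, so the damage is to significance testing and to the explanatory reading that {20b} intends. The upper end of the range rests on the whole drop-out allowance being baseline-filled and on an assumed mediator change that the article does not give. No size was worked out for NRS, muscle or brain measures. The primary comparison between arms is not touched by this point. It is worth correcting because the article states a fill rule without exemption and a single sentence closes the gap.

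**What to change.** Add to section {20b}: the correlations, and any mediation models, use only pairs of measures actually observed at the relevant visits, or a likelihood or multiple-imputation model; no carried-forward value enters them; they are run within arm or adjusted for arm; and the number of observed pairs is reported with each estimate. The same sentence should say whether the other results are analysed as changes.

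The cost is some precision. With about 132 pairs instead of a nominal 166, the detectable |r| at 80% power, tanh(2.80/√(n − 3)), moves from tanh(2.80/√163) = 0.22 to tanh(2.80/√129) = 0.24.

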##### Lumbar core muscle function assessment

TrA and LM muscle thickness will be directly measured by ultrasound, and the thickness change rate between the contractile and resting states will be calculated to predict the postural stability from the perspective of muscle morphology [28]. Images of the LM and TrA will be acquired in B-mode with a portable ultrasound machine (KONICA MINOLTA Inc., SONIMAGE HS1, Japan). Images of the resting and contractile states of the TrA and LM at the L4 level will be taken by a physician familiar with musculoskeletal ultrasound.

For bilateral TrA muscles, maximum expiration will be performed while the participants maintained in a crook lying position. The muscle thickness will be measured while maximum expiration is maintained for 3–5 s. The TrA muscle will be measured three times, and the average value will be calculated [9]. Tree images on bilateral LM will be taken at rest to measure the thickness and cross-sectional area in a prone position. Next, participants will be asked to lift their limbs about 5 cm straight off the table for 3–5 s. Once a clear image of the LM is obtained, it will be frozen on the screen and saved [29].

The average resting and contractile thickness of the TrA and LM will be calculated using the ImageJ software (Media Cybernetics, Silver Spring, USA). The following calculation formula of muscle contraction rate will be used: contraction rate = (average contraction thickness − average resting thickness)/average resting thickness × 100%.

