**Potential mediators**				
Pain catastrophizing (PCS)	X		X	X
Pain acceptance (CAPQ-8)	X		X	X
Pain Self-Efficiency Questionnaire (PSEQ)	X		X	X
Self-compassion (SCS)	X		X	X

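### Correlations with no stated time order or adjustment for arm or baseline are meant to identify the reasons for change, but cannot establish the mediation that Hypothesis 1 and the mediator section imply

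*Protocol article*

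**What the plan says.** The protocol article, under methods for additional analyses {20b}, fixes a method and a purpose. The method: "Changes in the primary outcomes (RMDQ and NRS) will be correlated with other results (deep trunk muscle function, brain function, and potential mediators"). The purpose: "to identify the reasons behind any change in the primary outcomes". It gives no time point, does not say whether the other results enter as change scores, and mentions neither arm nor baseline values.

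Two other sections show that the question is one of mediation:

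- Objectives {7}, Hypothesis 1, sets out a chain: SCT lowers negative emotion and raises adherence to the exercises, and through these reduces pain and disability.
- The section on potential mediators (PCS, CPAQ-8, PSEQ, SCS) says that "the effects of all potential mediators on the outcomes will be explored in both treatment groups", and names no model.

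On timing, "The potential mediators of outcome will be assessed at baseline and at 4 and 16 weeks after randomization". For the outcomes, "Participants will complete the outcome assessment at baseline, the end of the 4th week, and the follow-up 16 weeks after baseline evaluation". Table 3 gives the same three time points for GAD-7, PHQ-9, brain function and the musculoskeletal assessment. It records exercise adherence over weeks 1–4 and again at weeks 4 and 16.

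On mode of measurement, "Participants scanned the QR code to complete the questionnaire by themselves", whereas "TrA and LM muscle thickness will be directly measured by ultrasound", and brain function is assessed by MRI.

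**The concern.** A correlation between improvement in disability and some other measure is compatible with several explanations: the measure drives disability, disability drives the measure, both respond separately to treatment, or both reflect something else about the patient. Only the first is a reason for the change. Telling them apart needs at least the effect of arm on the mediator, a mediator measured before the outcome, and adjustment for arm and baseline. The stated method names none of these.

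The likely false explanation depends on the measure:

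- **Questionnaire mediators.** Patients complete these themselves on the same visit schedule as RMDQ and NRS. Mood or response style on the day can move both scores together.
- **Ultrasound and fMRI.** Shared reporting does not arise. The problem is confounding, including by arm: if treatment shifts both the measure and RMDQ, pooling the arms produces a correlation even when the two are unrelated within each arm.

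At stake is what the trial says about why SCT works. Followed literally, the plan would present associations as reasons.

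**Working it through.** The documents give no figure for the mechanism analysis, so there is none to reproduce. The calculations below illustrate the principle. The shared fractions and arm effects are assumptions.

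**Inputs from the protocol.** Sample size {14}: 66 per arm before dropout, so 132 completers; RMDQ change 5.5 (SD 4.7) against 3.1 (SD 4.8). Pooled SD = √[(4.7² + 4.8²)/2] = 4.75. Standardised arm effect = (5.5 − 3.1)/4.75 = 0.505. An assumed effect of 0.5 is therefore in line with the trial's own planning.

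**1. Shared reporting state, no mediation (questionnaire mediators).** Let each score at a visit be 0.7 × a stable trait + 0.7 × a visit-specific part. Traits are independent between mediator and outcome. A fraction f of the visit-specific variance is common to both at the same visit. The mediator has no effect on the outcome. In a baseline-to-week-16 change the trait cancels, leaving within-arm variance V = 2 × 0.7² = 0.98 and covariance f × 0.98.

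- No treatment effect: r = f.
- Treatment effect δ = 0.5 on each variable, arms pooled: r = (0.98f + δ²/4)/(0.98 + δ²/4) = (0.98f + 0.0625)/1.0425.

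Simulation, 2000 trials per row, 66 per arm, two-sided 0.05:

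| f (assumed) | mean r, no effect | significant | mean r, effect 0.5 | significant |
|---|---|---|---|---|
| 0 | 0.00 | 5% | 0.06 | 10% |
| 0.20 | 0.20 | 63% | 0.25 | 83% |
| 0.35 | 0.35 | 99% | 0.39 | 100% |
| 0.50 | 0.50 | 100% | 0.53 | 100% |

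Check with Fisher's z at f = 0.20 and no treatment effect: atanh(0.20) × √129 = 0.2027 × 11.36 = 2.30; P(Z > 1.96 − 2.30) = 63%, as simulated.

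**2. Confounding by arm only (also applies to ultrasound and fMRI).** Take a measure unrelated to RMDQ within arm, with an assumed 0.5 SD arm effect, and the protocol's 0.505 SD effect on RMDQ change. Pooled over 1:1 arms:

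r = 0.25 × 0.5 × 0.505 / √[(1 + 0.25 × 0.5²)(1 + 0.25 × 0.505²)] = 0.0631/1.063 = 0.059.

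This is significant in about 10% of trials with 132 patients and about 12% with 166, against 5% nominal. Within-arm or arm-adjusted correlations remove this component.

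**3. Time-ordered model under the same null.** Week-16 outcome regressed on week-4 mediator, arm, baseline mediator and baseline outcome, with treatment effect 0.5. Percentage of trials in which the mediator term is significant:

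| f (assumed) | adjusted as above | also adjusted for week-4 outcome |
|---|---|---|
| 0 | 6% | 5% |
| 0.20 | 7% | 6% |
| 0.35 | 12% | 7% |
| 0.50 | 17% | 10% |

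The time-ordered model removes most of the false signal but not all of it. Even with the week-4 outcome added, the rate at f = 0.50 is twice nominal.

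**The case against.** The strongest reply is that the analysis is additional. The mediator section speaks of exploring, Objective 2 is itself exploratory, no primary or secondary comparison depends on the result, and a journal article commonly leaves timing, covariates and the mediation model to the analysis plan. That stands as far as missing detail goes. It does not cover the stated purpose: the article itself pairs a correlation with identifying reasons, and no added detail makes a correlation a test of mediation.

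A reader might infer more than the text supports:

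- **That the plan commits to same-interval change-score correlations.** Section {20b} fixes change only for RMDQ and NRS and gives no timing. The rates in step 1 hold only if both sides are changes over the same interval.
- **That the plan ignores arm.** It is silent in {20b}, and exploring mediator effects in both treatment groups may mean analysis by arm. Step 2 applies only if arms are pooled.
- **That shared reporting contaminates most of the correlations.** It applies to the questionnaire mediators. The several ultrasound measures and fMRI are outside it.
- **That the trial has a known false-positive rate near 100%.** The shared fractions come from no document. The range shows a mechanism and does not estimate this trial's error.
- **That the data are already in hand.** They are scheduled; the trial status section expects recruitment to run to October 2023.
- **That a model using only SCS, PCS, CPAQ-8 and PSEQ would test Hypothesis 1.** That hypothesis concerns negative emotion and adherence, which GAD-7, PHQ-9 and the home practice diary measure.

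**Conclusion.** The point holds in limited form. Section {20b} assigns correlations an explanatory purpose they cannot serve, for a question that Objectives {7} and the mediator section frame as mediation. This rests on stated text. The qualitative conclusion needs no simulation. The size does: if changes are taken over the same interval and the visit-specific shared fraction is 20–50%, questionnaire correlations would be significant in 63–100% of trials without mediation. With no shared state, but pooled arms and arm effects of about 0.5 SD, the figure is about 10%. The matter is worth correcting but secondary: it concerns the interpretation of an additional analysis and leaves the primary comparison untouched.

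**What to change.** **Wording.** Report the {20b} correlations as exploratory associations, within arm or adjusted for arm, and drop the claim that they identify reasons.

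**Mechanism analysis.** Specify an exploratory, time-ordered mediation model on the scheduled data:

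1. Arm effect on the week-4 mediator, adjusted for its baseline. Mediators: GAD-7 and PHQ-9 (the emotion part of Hypothesis 1), SCS, PCS, CPAQ-8 and PSEQ, plus exercise adherence over weeks 1–4, which has no baseline value to adjust for.
2. Week-16 RMDQ, and likewise NRS, on arm, week-4 mediator, baseline mediator and baseline outcome, with a sensitivity analysis adding the week-4 outcome.
3. The indirect effect with a bootstrap interval.

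The same model can take the week-4 muscle and brain measures.

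**Cost.** A change of wording and a little more analysis; no new data. Week-4 mediators may miss mechanisms that act later. Unmeasured mediator–outcome confounding and some residual shared-state inflation remain (up to 17% in step 3, or 10% with the week-4 outcome added, at the largest assumed fraction) and should be stated as limitations.
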